**Objective:**

The objective of this open-label pilot clinical trial is to test the feasibility and safety of intranasal ketamine in patients who have not responded to electroconvulsive therapy. The primary outcome is to determine the feasibility of a larger randomized controlled trial to test the efficacy of intranasal ketamine for patients who have not responded to electroconvulsive therapy for clinical indicators in unipolar depression. The secondary outcome is to determine the preliminary effects of an intervention on clinical outcomes, such as depressive symptoms, suicidal ideation, and quality of living. The third outcome is to explore neurophysiological changes as measured by transcranial magnetic stimulation electromyography and electroencephalography to measure changes in cortical excitability as potential predictors of clinical response.

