In this study, we aim to assess the safety and feasibility of intranasal rketamine in patients with unipolar depression who did not respond to the acute course of electroconvulsive therapy to inform a larger randomized controlled trial and examine potential neurophysiological biomarkers of response. TMS- electromyography (EMG) and electroencephalography (EEG) paradigms can be used to investigate the impact of ketamine on cortical activities via intracortical facilitation and short-interval cortical inhibition paradigms [19,22-26]. Based on accumulating evidence supporting the efficacy and tolerability of ketamine, we hypothesize that intranasal rketamine administered twice per week over 4 weeks will (1) result in improvement in depressive; (2) be safe and well tolerated in patients with treatment-resistant depression who could not tolerate or have not responded to electroconvulsive therapy; (3) result in neurophysiological changes. The results of this study will provide an important characterization of the neurophysiological effects of rketamine on cortical neurophysiology [19,22-26], which may serve as a ketamine biomarker and would be a crucial breakthrough in determining potential predictors of clinical response for depression.

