## Methods

### Design

This is an open-label pilot study to assess the feasibility of conducting a randomized controlled trial to test the safety, tolerability, and efficacy of intranasal ketamine in patients with treatment-resistant depression who did not respond or were not able to tolerate a course of acute electroconvulsive therapy.

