Monitoring assessment during treatment sessions will include (1) vital signs collected every 30 minutes during a 2-hour monitoring session (blood pressure, heart rate, and oxygen levels) and (2) behavior changes assessed through observation.

Neurophysiological assessments will include (1) the Transcranial Magnetic Stimulation Adult Safety Screen to assess for potential TMS risk factors; and (2) TMS-EMG/EEG (Multimedia Appendix 2). Our neurophysiological measures have been established and have a high test–retest reliability (ie, intraclass correlation >0.9) [31,32]. Data analysis will be performed using semiautomated methods developed and validated by our group [31,32]. TMS pulses will be administered to the left dorsolateral prefrontal cortex, using a figure-of-eight coil (7 cm), and 2 Magstim 200 stimulators (Magstim Company Ltd) connected via a Bistim module, and motor evoked potential data will be collected using commercially available software (Signal, Cambridge Electronics). Each TMS session will include the establishment of the individual threshold for stimulation motor cortex, and dorsolateral prefrontal cortex localization will be performed according to previously published methods [31,32]. Resting motor threshold will be determined by applying single pulses of TMS to the motor cortex while the coil is placed at the optimal position to elicit motor evoked potentials from the right abductor pollicis brevis muscle. The resting motor threshold is defined as the minimum stimulus intensity that elicits a motor evoked potential of >50 μV in more than 5 of the 10 trials [33,34]. Electromyography will be recorded from the abductor pollicis brevis with Ag–AgCl electrodes placed over the belly of the muscle. The signal will be amplified (Intronix Technologies Corporation Model 2024F), filtered (bandpass 2 Hz-5 kHz), digitized at 5 kHz (Micro 1401, Cambridge Electronics Design), and stored in a laboratory computer for offline analysis. The participants will be instructed to relax throughout the study. Trials contaminated with voluntary muscle activity will be discarded.

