### Statistical Analysis

#### Statistical and Analytical Plans

Baseline participant characteristics will be reported and described using summary statistics—mean and standard deviation for continuous data and number and proportion for categorical data. The primary analysis to determine if there is a statistically significant effect of intranasal ketamine on depressive symptoms will be the paired 1-tailed *t* test of the HDRS-24 score at baseline to week 4. We will also report the standardized mean difference as a measure of effect size (small: 0.2; medium: 0.5; large: 0.8 [40]). For tolerability and safety outcomes, we will report the number and proportion of individuals who experience a transient increase in blood pressure, agitation, and behavioral disturbance. To assess suicidality change, we will use the 1-tailed paired *t* test from baseline to week 4 of the Scale of Suicide Ideation score and calculate the standardized mean difference. For neurophysiology, we will use the 1-tailed independent *t* test to compare components of TMS-evoked responses at left dorsolateral prefrontal cortex. In addition, we will use the nonparametric cluster-based permutation test to investigate any significant changes in overall EEG channels.

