## Discussion

To our knowledge, this is the first study to test repeated doses of rketamine delivered intranasally in patients with major depressive disorder who did not respond (either clinically or due to their inability to tolerate) to an acute course of electroconvulsive therapy. The use of neurophysiological tools to assess changes in cortical excitability will provide preliminary data for potential biomarkers of response, which can be further assessed in a larger clinical trial. A lack of control group and small sample size are limitations of the current protocol. However, given that it is a pilot open-label clinical trial, the sample size is sufficient (ie, the goal is not to assess generalizability or statistical significance). The lack of blinding in the control group is a common concern in ketamine trials [27], because a placebo with comparable effects does not exist, and it is impossible to ensure blinding to the full extent. Because the study is being conducted at a single site of a large psychiatric academic facility, the results may not be transferable to a broader population.

Results will be presented during scientific conferences, in clinical rounds, and publications in relevant journals.

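### An independent t test is named for the TMS-evoked responses without a contrast, although the trial has one arm and hypothesises within-patient change; for that comparison the test should be paired

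*Protocol article*

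**What the plan says.** All places are in the protocol article.

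- **Statistical and Analytical Plans:** "we will use the 1-tailed independent *t* test to compare components of TMS-evoked responses at left dorsolateral prefrontal cortex". Neither groups nor time points are named. The HDRS-24 and the Scale of Suicide Ideation, in the same paragraph, each get a one-tailed paired t test from baseline to week 4. The sentence after the TMS test is also about change: "we will use the nonparametric cluster-based permutation test to investigate any significant changes in overall EEG channels".
- **Design:** "This is an open-label pilot study to assess the feasibility of conducting a randomized controlled trial". **Discussion:** "A lack of control group and small sample size are limitations of the current protocol".
- **Abstract, Objective:** the aim listed third reads "explore neurophysiological changes as measured by transcranial magnetic stimulation electromyography and electroencephalography to measure changes in cortical excitability as potential predictors of clinical response".
- **Introduction:** the last of the numbered hypotheses is that treatment will "3) result in neurophysiological changes".
- **Study Measurements:** the neurophysiological measures "have a high test–retest reliability (ie, intraclass correlation >0.9". The section refers to each TMS session, so more than one session per patient is implied. The visit schedule is in Multimedia Appendix 2, which is not shown.

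**The concern.** An independent t test compares two unrelated samples. This trial enrols one group, and its neurophysiology hypothesis is about change in that group. The natural comparison is therefore each patient's TMS-evoked components before and after treatment. Those values are paired, and an independent test ignores the pairing.

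When repeated values are positively correlated, the independent test counts the stable differences between patients as error. The standard error and p value are then too large. A real effect of ketamine on cortical responses could be reported as no effect, which matters because candidate neurophysiological markers are one of the two products the Conclusions promise for later work. A full analysis plan may add detail to this sentence, but the article does more than leave detail out: it names a specific test, and that test does not fit the stated hypothesis.

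**Working it through.** **Inputs.** n = 25, one site (Recruitment). One arm, no control group (Design; Discussion). One-tailed test (Statistical and Analytical Plans). Assumed, because the article does not give them: 5% significance level, equal SDs before and after, normal data, pre-post correlation r from 0 to 0.9, and a true change of d baseline SDs.

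**The plan's own figure.** No power, SD or effect size is stated for this test. The sample size is a recruitment figure and reproduces at its lower bound: 250 per year × 0.25 × 0.20 × 2 years = 25.

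**Standard error.** For a mean change in n patients with SD σ:

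- true variance = 2σ²(1−r)/n
- variance used by the independent test = 2σ²/n
- ratio of standard errors = 1/√(1−r)

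With n = 25 the independent test uses √(2/25) = 0.283σ whatever r is. The true value is √(2 × 0.5/25) = 0.200σ at r = 0.5 and √(2 × 0.1/25) = 0.089σ at r = 0.9.

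**Power and type I error.** Paired power comes from the noncentral t distribution with 24 df and noncentrality d√n/√(2(1−r)). For d = 0.3 this is 0.3 × 5/√1 = 1.50 at r = 0.5 and 0.3 × 5/√0.2 = 3.35 at r = 0.9. Rejection rates of the independent test (48 df) were simulated with 100,000 replicates. The simulation also confirmed the paired values.

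| r | SE too large by | Actual type I error, independent (nominal 5%) | Power, d = 0.3: paired / independent | Power, d = 0.5: paired / independent |
|---|---|---|---|---|
| 0 | 1.00 | 5.0% | 27% / 27% | 53% / 54% |
| 0.3 | 1.20 | 2.5% | 34% / 24% | 66% / 55% |
| 0.5 | 1.41 | 1.1% | 43% / 20% | 78% / 55% |
| 0.7 | 1.83 | 0.2% | 59% / 15% | 93% / 57% |
| 0.9 | 3.16 | about 0% | 95% / 6% | >99.9% / 61% |

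**Change detectable with 80% power**, paired versus independent (the latter by a normal approximation): 0.61 versus 0.67 SD at r = 0.3, 0.51 versus 0.64 at r = 0.5, 0.40 versus 0.61 at r = 0.7, and 0.23 versus 0.55 at r = 0.9.

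The loss is nil at r = 0, modest at r = 0.3 and severe near 0.9. It is largest for small changes.

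**The case against.** **The contrast is not stated.** An independent test would be valid for responders versus nonresponders, which would suit the interest in predictors of response. The article also distinguishes patients who did not respond to electroconvulsive therapy from those who could not tolerate it. So it is too much to say that no two groups could be formed. This stands. But neither split is tied to this test, and a test of either would not address the hypothesis of change. The sentence needs correcting on either reading.

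**The correlation is unknown.** A reader might infer from the quoted reliability that the pre-post correlation exceeds 0.9, and that real changes will therefore be missed. The article does not support this. Test-retest reliability is not the correlation between baseline and post-treatment values under ketamine, which may be lower if patients change by different amounts. Nor does the article say that the figure applies to prefrontal EEG components rather than motor EMG measures. The r = 0.9 row is one end of a range, and changes above roughly 0.6 SD would usually be found even with the independent test.

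**The outcome is exploratory.** It is third in order, and the Discussion disclaims statistical significance as a goal. With r at or above zero the error does not raise the false-positive rate above nominal, and the feasibility, safety and depression results are untouched. This lowers the severity. It does not make the test right.

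**Related gaps.** A reader might also fault the absence of a definition of response or of an analysis linking the measures to response, or might assume that the permutation test is unpaired. A condensed article may leave the first two to the analysis plan, and it does not say whether the permutation test is paired. None of these is part of this point.

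**Conclusion.** The point holds in a limited form. The article names an independent t test with no contrast, in a one-arm trial whose hypothesis is within-patient change and whose two sibling outcomes are tested as paired. Applied to before-after data, the test would overstate the standard error by 1.20 to 3.16 times for r from 0.3 to 0.9, and for a 0.3 SD change it would cost between 10 (34% − 24%) and 89 (95% − 6%) percentage points of power. At r = 0 it costs nothing. Real changes may be missed; the article does not show that they will be.

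These figures assume the before-after reading, 25 complete pairs, equal SDs, normal data and a one-sided 5% level. Severity: should be fixed. The outcome is exploratory, the error is in the conservative direction, and the paired data would remain available for a correct analysis.

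**What to change.** Name the contrast and make the test paired. For example: *Components of the TMS-evoked response at the left dorsolateral prefrontal cortex will be compared between baseline and the post-treatment assessment with a paired t test, and the mean change will be reported with its 95% confidence interval.* The post-treatment visit should be the one in the study schedule.

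If a comparison between patients is also wanted, such as responders versus nonresponders, state it as a separate analysis with its groups defined. The independent t test belongs there.

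The cost is one sentence in the analysis section, with no new data, visits or change in sample size.

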#### Sample Size

CAMH treats approximately 250 new patients with depression each year with electroconvulsive therapy. Assuming 25% to 30% nonresponse or intolerability and that, of these individuals, 20% will be eligible for treatment, we expect to be able to recruit 25 participants over the course of 24 months.

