#### Feasibility

We believe recruiting 25 participants over the course of 2 years is feasible. Participants will be recruited through the Temerty Centre for Brain Intervention at CAMH, which treats approximately 150 to 200 patients with depression with electroconvulsive therapy per year. The principal investigator is a staff psychiatrist at the Mood and Anxiety Division, which provides outpatient services for a large population with mood disorders at local and provincial levels. In addition, this protocol has been piloted with 3 patients who were nonresponsive to electroconvulsive therapy, and the patients were able to comply with a protocol of 2 sessions per week for 8 treatment sessions given very close clinical supervision in a trial (unpublished data, [name]).

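### The 25 participants expected in 24 months rest on about 250 ECT patients a year, but the stated recruitment centre's 150 to 200 a year gives 15 to 24

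*Protocol article*

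**What the plan says.** The Sample Size section under Statistical Analysis is an accrual calculation. It starts from a yearly volume: "CAMH treats approximately 250 new patients with depression each year with electroconvulsive therapy". It then applies two fractions, "Assuming 25% to 30% nonresponse or intolerability" and "of these individuals, 20% will be eligible for treatment", and concludes "we expect to be able to recruit 25 participants over the course of 24 months". It contains no power or precision argument.

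The Feasibility section under Recruitment and Feasibility defends the same target: "We believe recruiting 25 participants over the course of 2 years is feasible". It names the route, "Participants will be recruited through the Temerty Centre for Brain Intervention at CAMH", and gives that centre's volume: "which treats approximately 150 to 200 patients with depression with electroconvulsive therapy per year". It then mentions the principal investigator's post in the hospital's Mood and Anxiety Division and that division's outpatient service, without a count of ECT patients. The Recruitment section names CAMH as the one site.

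No part of the article explains how the two annual volumes relate.

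**The concern.** Two sections support one claim with two different starting volumes, and the accrual calculation uses the larger. The section that says where participants will come from gives the smaller. If the smaller volume is the real base, the protocol's own fractions do not produce 25 in 24 months.

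The wording adds to the doubt. The larger figure is limited to new patients and the smaller is not. For one and the same service, a count of new patients would normally be no larger than the count of all patients treated.

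What is at stake is a planning figure. The accrual estimate is the only derivation of 25 in the Sample Size section, and the article's primary outcome is the feasibility of a larger randomized trial. The article does not list recruitment rate as a feasibility measure, so its weight there is an inference. Even so, the two volumes give different expectations (25 to 30, or 15 to 24), and nobody can say whether accrual is on plan until one is chosen.

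**Working it through.** **Inputs, all from the article**
- Annual ECT volume: 250 (Sample Size); 150 to 200 (Feasibility).
- Nonresponse or intolerance: 0.25 to 0.30 (Sample Size).
- Share of those who are eligible: 0.20 (Sample Size).
- Recruitment period: 24 months, or 2 years (both sections).

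**Formulas**
- Eligible in 24 months = annual volume × nonresponse fraction × 0.20 × 2.
- Months to reach 25 = 25 ÷ (annual volume × nonresponse fraction × 0.20) × 12.

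**Step 1: reproduce the stated figure.** 250 × 0.25 × 0.20 × 2 = 25. The stated 25 is recovered exactly at the lower nonresponse fraction. At the upper fraction, 250 × 0.30 × 0.20 × 2 = 30.

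**Step 2: put in the Feasibility volume.** The fractions are unchanged.

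| Patients a year | Nonresponse fraction | Eligible in 24 months | Months to reach 25 |
|---|---|---|---|
| 150 | 0.25 | 15 | 40.0 |
| 150 | 0.30 | 18 | 33.3 |
| 200 | 0.25 | 20 | 30.0 |
| 200 | 0.30 | 24 | 25.0 |
| 250 | 0.25 | 25 | 24.0 |
| 250 | 0.30 | 30 | 20.0 |

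All four combinations at 150 to 200 a year fall below 25. The shortfall runs from 25 − 24 = 1 to 25 − 15 = 10.

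**Step 3: find the volume that 25 requires.** Required volume = 25 ÷ (2 × 0.20 × nonresponse fraction).
- At 0.25: 25 ÷ 0.100 = 250 a year.
- At 0.30: 25 ÷ 0.120 = 208.3 a year.

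Both lie above 200.

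**Step 4: check for slack.** The formula counts eligible patients, and the section treats them as recruited. At 250 a year and 0.25 there are exactly 25 eligible patients for 25 places, so every one must consent. Refusals would lower every count in the table.

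**The case against.** Four points on the other side deserve weight.

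- **The denominators may differ.** The 250 is attached to the hospital and the 150 to 200 to a named centre within it, and one counts new patients while the other counts patients. Both could be true. This stands as a possibility, so the larger figure is not shown to be wrong. But the article does not offer this explanation, and it names the smaller unit as the recruitment route, so the use of 250 still needs to be justified.
- **Other sources could add participants.** Feasibility mentions a large outpatient service, and the inclusion criteria do not require that ECT was given at this hospital or after the trial opened. This also stands. A reader might infer from the table that the trial will miss its target, but the documents do not support that: 15 to 24 is what one stated volume yields, not a ceiling on accrual. The extra sources are not quantified, however, so they cannot support the figure of 25 either.
- **The best case is nearly enough.** With 200 a year and 30%, the yield is 24, and both volumes are given as approximate. A reader might infer that 25 can be reached only with 250 a year. That is too strong, because about 208 a year is enough at 30%. The gap is material at the middle and lower inputs, where the yield is 15 to 20.
- **It is a pilot and the analysis does not depend on the volume.** The Discussion defends the sample size separately, on the ground that a pilot does not aim at generalizability or statistical significance. No test depends on 250, and a later trial could plan from the accrual actually observed. This limits the consequence but does not remove the inconsistency.

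**Conclusion.** The concern holds as an unreconciled planning figure. The 25 in 24 months follows from 250 patients a year at 25% nonresponse or intolerance. The volume given for the stated recruitment centre yields 15 to 24 under the same fractions, or 25 to 40 months to reach 25, and no combination in that range reaches the target in 24 months. The shortfall is 1 to 10 participants.

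This rests on the article's own fractions, on a steady yearly flow, on the named centre as the only source, and on consent from every eligible patient. It does not show which volume is correct, nor that recruitment will fail. No analysis is affected.

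**What to change.** Reconcile Feasibility and Sample Size to one annual count for the source from which participants will actually be recruited, and say whether it covers the hospital or the centre and new or all ECT patients. If other referral sources are relied on, name them and state what they are expected to contribute.

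Then restate the expected 24-month accrual or the recruitment period from that count, and note that the calculation assumes all eligible patients consent.
- If 150 to 200 a year is the right base, state 15 to 24 participants in 24 months before refusals, or 25 to 40 months for 25 participants.
- If 250 a year is right, correct or explain the Feasibility figure, and note that the lower case leaves no room for refusals.

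The cost is a change of text in two sections and possibly a less favourable forecast. No increase in enrolment is needed.

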## Results

This study has received ethics approval. We have started recruitment for the trial and anticipate having initial results in spring 2022.

## Discussion

To our knowledge, this is the first study to test repeated doses of rketamine delivered intranasally in patients with major depressive disorder who did not respond (either clinically or due to their inability to tolerate) to an acute course of electroconvulsive therapy. The use of neurophysiological tools to assess changes in cortical excitability will provide preliminary data for potential biomarkers of response, which can be further assessed in a larger clinical trial. A lack of control group and small sample size are limitations of the current protocol. However, given that it is a pilot open-label clinical trial, the sample size is sufficient (ie, the goal is not to assess generalizability or statistical significance). The lack of blinding in the control group is a common concern in ketamine trials [27], because a placebo with comparable effects does not exist, and it is impossible to ensure blinding to the full extent. Because the study is being conducted at a single site of a large psychiatric academic facility, the results may not be transferable to a broader population.

Results will be presented during scientific conferences, in clinical rounds, and publications in relevant journals.

